#### Risk of falls

Falls are common in older adults, and although steps can be taken to prevent falls, this is not always possible. When performing tests of mobility, the investigator will be responsible for first assessing that the environment is safe (e.g., the floor is not slippery, no obstacles present, the participant is wearing appropriate footwear and sensory aids if necessary, walking aids are provided if needed). If either the investigator or the participant do not feel safe to perform any tests of physical performance then they will not proceed to do so, and this will be documented on the CRF. If the participant does fall, then the investigator will abide by the Queen Elizabeth Hospital Birmingham site policy for manual handling and care of the falling patient. A clinical assessment will then be performed by the investigator to assess for injury and cause for fall. This will be documented in their medical notes, communicated to the usual care team, and an incident form sent as per trust policy.

#### Venepuncture

Participants may find venepuncture uncomfortable, and this may leave a bruise afterwards. A maximum of 70mL of blood will be taken at any time. Some participants may feel faint following having venepuncture performed. Vasovagal syncope (feeling faint whilst having blood taken) is by definition self-limiting so will resolve spontaneously. We will minimise the risk of vasovagal syncope occurring by ensuring the participant’s have blood taken in the specially designed phlebotomy chair at the Institute of Inflammation and Ageing which keeps the feet elevated during phlebotomy. It is also possible to lie the participant flat in the phlebotomy chair so should a vasovagal syncope episode occur it can be resolved quickly by restoring blood flow to the brain.

#### Adipose biopsies

The risks of these procedure are pain, infection, bleeding and local nerve damage (rare). Pain following the procedure will be minimised by using local anaesthetic and advising participants to take simple analgesia such as paracetamol afterwards. Aseptic technique using a sterile field and gloves will be used to minimise the risk of infection. The procedure will not be performed on participants who are taking anticoagulants or clopidogrel, or who have a known bleeding disorder.

*Medical Emergencies*

The Clinical Visits will all occur at the Clinical Research Facility at the University of Birmingham which is located within the Queen Elizabeth Hospital Birmingham. Staff are trained in the recognition and management of medical emergencies and there are procedures in place to manage medical emergencies which may take place during any study or study visit. If required the management of an unwell participant can be escalated to include the NHS medical crash team and a participant can be transferred to an NHS location in the Queen Elizabeth Hospital Birmingham for further assessment and management.

*Electroencephalography*

The risks associated with the saline-based EEG are minimal. Participants may find the task-based EEG slightly tedious due to its repetitive nature, but no significant discomfort is expected.

Diagnosis of previously unknown conditions

Conditions that were previously unknown to the participant may be identified during the process of research data collection; this could be considered both a beneficial and unfavourable consequence. In the case of potentially significant findings, these will be explained to the participant, including the potential consequences and further investigations or treatment that might be indicated. These findings will be relayed to the participants’ General Practitioners (GP) or secondary care medical team, who will be advised to arrange further management or to refer to appropriate specialties; this is usual practice in the United Kingdom (UK). Specific consent for findings to be communicated with their GP or medical team will be gained from the participant; the GP will be informed routinely of recruitment to this study. As the researchers will have a dual role as clinicians working within the NHS trust, it may sometimes be appropriate for the clinicians to arrange further investigations, management, or follow-up, but such decisions should be clearly communicated to the wider NHS team. It should be clarified to the participant that any investigations or management are separate from the research study and are part of NHS care.

The study will fit within existing ethical and regulatory frameworks. Participants are healthy volunteers, and not recruited as NHS patients. However, as the recruitment and assessments will take place within an NHS institution we will secure approval through the Health Research Authority (HRA) and an NHS Research Ethics Committee (REC).

Drug Intervention

Metformin has a long history of use in older adults and the safety profile is good (6). Metformin will be used off-licence. It is licensed only for use in type 2 diabetes but is also commonly used for polycystic ovary syndrome and type 1 diabetes. The drug will be started slowly and the target dose reached over a week to minimise side effects. There will be a telephone call after a week to assess any side effects and to decide whether to continue with the intervention or to withdraw the participant from the study. Spermidine and fisetin are supplements which are available “over the counter” in the UK. The doses have been chosen to mimic doses in recent studies (ref – Senokowitsch, 2023) and also available supplements. There are no known side effects reported in the literature (Wu, 2020, spermidine – a comprehensive review of spermidine)(9).

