- Does a three week course of metformin, spermidine, or fisetin reduce mTOR activation in healthy older volunteers?

Outcomes

Primary Outcome

- Number of senescent cells in adipose tissue measured by SA-β-GAL technique after three weeks of intervention, adjusted for baseline number of senescent cells prior to the intervention.

Secondary Outcomes

- Senescent cell burden in adipose tissue as measured by transcriptomics using SenMayo analysis after three weeks of intervention, adjusted for baseline number of senescent cell burden prior to the intervention.
- Epigenetic age (DNA methylation) after three weeks of intervention, adjusted for baseline epigenetic age prior to the intervention.
- Immunesenescence as measured by IMM-AGE analysis after three weeks of intervention, adjusted for baseline IMM-AGE prior to the intervention.
- Autopahgic flux as measured by flow cytometry after three weeks of intervention, adjusted for autophagic flux prior to the intervention.
- Nutrient sensing as measured by mTOR activation after three weeks of intervention, adjusted for baseline nutrient sensing prior to the intervention.
- Mitochondrial function as measured by Seahorse after three weeks of intervention, adjusted for baseline mitochondrial function prior to the intervention.
- Inflammation as measured by ELISA and multiplex technology after three weeks of intervention, adjusted for baseline inflammation prior to the intervention.
- Microbial composition and functional potential of stool using metagenomics after three weeks of intervention, adjusted for baseline microbial composition and functional potential prior to the intervention.
- Changes in neural oscillatory signatures measured by EEG.

1. Study design and methods of data collection and data analysis

This study is a Phase 2a clinical study. It is designed to investigate the effect of the intervention, metformin, spermidine, or fisetin, on biological outcomes. Additionally, an embedded qualitative interview sub-study will be undertaken with a sub-sample of participants enrolled in the REPROGRAM trial. See section 8 for information about the qualitative sub-study.

Power Calculations

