| Stool collection | X |  |  |  | X |  |
| EEG | X |  |  |  | X |  |
| Venepuncture | X | X |  |  | X |  |
| Adipose biopsies |  | X |  |  | X |  |
| Adverse event reporting | X | X | X | X | X |  |
| Drug distribution |  | X |  |  |  |  |
| Compliancy pill count |  |  |  |  | X |  |
| Qualitative Interview |  |  |  |  |  | X |

Co-morbidities and medications

Co-morbidities and medications will be recorded using check boxes for frequently encountered conditions and medications with the option for free text to record less common co-morbidities and medications.

Handgrip strength

Handgrip strength will be measured using a handheld dynamometer (Jamar, Takei Grip D, or other calibrated device). Where the participant can sit out in a chair, handgrip strength will be measured with the arm flexed at 90^O^ at the elbow and the forearm supinated. If the participant cannot sit out and measurements are taken in the bed, this will be recorded and measurements will instead be performed in the most upright position that is feasible. Participants will be asked to “squeeze as hard as [they] can”. Handgrip strength will be measured twice on each side and the best recording of all will be used for analysis (29).

Short physical performance battery

The Short Physical Performance Battery (SPPB) is a standardised measure of physical performance that has been shown to be sensitive to change and provides an objective measure of physical function (30). SPPB consists of usual gait speed, side-by-side stand, semi-tandem stand, tandem stand, and five chair stands. A total score of 12 is derived, with a lower score representing reduced physical performance. SPPB will be measured within 48 hours of admission and 48 hours of discharge. Gait speed will be measured by asking the participants to walk a four-metre course at their “usual pace”. Participants will be asked to complete five chair stands “as quickly as [they] can” (see Appendix). If it is not possible to measure gait speed or any part of the SPPB at any planned visit the reasons for this will be recorded (e.g., if either the investigator or the participant considers it unsafe to do so). The need or use of a mobility aid will be recorded. It is recommended that the SPPB should be performed after assessment of muscle quantity/quality (ultrasound quadriceps and bioelectrical impedance analysis), to ensure that these assessments are not affected the effect of exercise.

Activities of Daily Living (ADL) assessment

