Bioelectrical impedance analysis (BIA) will be measured at each visit using the Bodystat Quadscan 4000. This procedure will not be performed if the participant has an implanted permanent pacemaker or defibrillator. The investigator will determine if a cardiac device is present by asking the participant and/or consultee where possible, reviewing medical notes, including imaging where appropriate, and externally examining the participant. Participants with cardiac devices may still be included in the study, but this procedure will not be performed. Two electrodes will be placed on the right foot; one below the base of the toes and the other on the ankle between the medial and lateral malleoli. Electrodes will be placed sideways so that the non-stick electrode connector is facing the researcher. The red alligator clip will be attached to the electrode nearest the toes and the black to the one at the ankle. A further two electrodes will be placed on the right hand; one behind the knuckles and the other on the wrist next to the ulnar head. The red alligator clip will be attached to the electrode nearest the fingers and the black to the one at the wrist. Height and weight measurements should be obtained (these can be extracted from clinical records if available or measured by the research team). During hospitalisation, weight may be estimated if it is not possible to obtain new readings, but this should be documented by the research team. Key participant information (height, weight, age, sex) will be entered onto the device and results will appear on screen. All returned results will be recorded. This will include fat weight, lean weight, total body weight, dry lean weight, skeletal muscle mass (SMM), and extracellular water (ECW) and intracellular water (ICW).

Three-day food record

Participants will be supplied with a three-day food record at their research appointments and asked to complete this for the next three days. They will then post this back to the research team. This will be used to estimate daily calorific and protein intake at each assessment, adjusted for the participant’s weight at that timepoint.

Adverse Event Reporting

Participants will be asked about any adverse events that occurred during the study period. These will be recorded and reported appropriately. During the telephone call mid-way through the study intervention period participants may be excluded from continuing in the study.

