On day 7 all participants taking metformin will be rung and asked about side effects to the drug and to determine whether to withdraw the participant at this point or to increase the dose to the study dose of 1500mg for 21 days.

Drug Distribution

Participants will be supplied with the drugs they are taking for the study and counselled on possible side effects and the appropriate course of action. They will be supplied with all the drugs at the Day 0 Clinical Visit by a medical professional. The metformin will be prescribed by a study doctor and supplied by hospital pharmacy on the 2^nd^ research clinic visit. Spermidine and fisetin are nutraceuticals and therefore do not need a prescription. They will be supplied with instructions on how to take them.

Compliancy Pill Check

Participants will be asked to bring back the boxes and packets of the drugs they have been supplied with to check their adherence to the drugs during the study period. A member of the study team will check the boxes to see whether all the tablets have been taken. They will record the number of tablets left. They will also ask the participant if they took all their tablets as directed and if not why. The participants will also be asked to complete the drug record.

1. **REsilience and Frailty Research – Lived Experience of Community-dwelling Older AdulTs (REFLECT Study)**

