**Table 3 - Assessment and management of risk**

| **Intervention** | **Risks** | **Amelioration of Risk** |
| --- | --- | --- |
| Metformin MR | **Side effects as listed in British National Formulary (BNF)**  **Common or very common**  Abdominal pain; appetite decreased; diarrhoea; gastrointestinal disorder; nausea; taste altered; vitamin B12 deficiency; vomiting  **Rare or very rare**  Hepatitis; lactic acidosis (discontinue); skin reactions | Metformin MR will be started at a low dose of 500mg once a day as advised by BNF. This will reduce the risk of gastrointestinal side effects.  Participants with a diagnosis of symptomatic heart failure will be excluded to reduce the risk of lactic acidosis.  Vitamin B12 levels will be checked prior to commencing the drug intervention and following completion of the study to diagnose deficiency. Participants with a deficiency prior to starting will be excluded from participation.  Surveillance blood tests will be checked one week after discontinuing metformin MR to ensure there has been no impact on liver function. |
| Spermidine | No known side effects | Surveillance blood tests will be checked one week after discontinuing spermidine to ensure there has been no impact on organ function |
| Fisetin | No known side effects | Surveillance blood tests will be checked one week after discontinuing fisetin to ensure there has been no impact on organ function. |

Research Ethics Committee (REC) and other Regulatory review & reports

Before the start of the study, a favourable opinion will be sought from a REC (Research Ethics Committee) and the Health Research Authority (HRA) through the National Research Ethics Service for the study protocol, informed consent forms and other relevant documents. All correspondence with the REC will be retained. It is the Chief Investigator’s responsibility to produce the annual reports as required. The Chief Investigator will notify the REC of the end of the study. An annual progress report (APR) will be submitted to the REC within 30 days of the anniversary date on which the favourable opinion was given, and annually until the study is declared ended. If the study is ended prematurely, the Chief Investigator will notify the REC, including the reasons for the premature termination. Within one year after the end of the study, the Chief Investigator will submit a final report with the results, including any publications/abstracts, to the REC.

Regulatory Review & Compliance

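### Stopping the drug at a telephone call is treated as leaving the study, so those withdrawn have no post-treatment biopsy, and no scheduled visit delivers the post-discontinuation bloods that Table 3 promises

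*Protocol*

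**What the plan says.** Three places deal with what happens at the calls.

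- **Section 11, Drug Intervention** (metformin, call after one week): the purpose is "to decide whether to continue with the intervention or to withdraw the participant from the study".
- **Section 7, Adverse Event Reporting** (metformin, Day 7): the call is "to determine whether to withdraw the participant at this point or to increase the dose to the study dose of 1500mg for 21 days".
- **Section 7, Adverse Event Reporting** (all arms): "During the telephone call mid-way through the study intervention period participants may be excluded from continuing in the study". This is permissive and gives no criteria.

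The primary outcome is "Number of senescent cells in adipose tissue measured by SA-β-GAL technique after three weeks of intervention", adjusted for baseline. Table 2 places adipose biopsies at Day 0 and Day 28/35 only. It places venepuncture at the initial assessment, Day 0 and Day 28/35 only. It has no early-termination visit.

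Table 3 says of metformin: "Surveillance blood tests will be checked one week after discontinuing metformin MR to ensure there has been no impact on liver function". It makes the same promise for spermidine and fisetin with respect to organ function. None of the three entries is limited to participants who complete the course. The metformin entry also has vitamin B12 checked after the study is completed.

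Under Power Calculations, 9 participants are required and 10 of each sex are recruited to each drug to allow for dropout.

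**The concern.** Stopping a drug and leaving a study are different events, and the protocol merges them. Two things follow.

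First, a participant withdrawn at a call has a baseline biopsy and no second one, and so no primary outcome. The remaining tissue comes from a group selected after treatment began. In the metformin arm the selection has an additional step that depends on side effects, and section 9 of the protocol calls diarrhoea a commonly reported side effect of that drug. This is a data-collection rule, so a later analysis plan cannot repair it: it cannot analyse a biopsy that was never taken.

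Second, the participants whose safety matters most at that moment are those who stop because of side effects. Table 3 intends bloods for them, but no visit exists at which to take them, and the participant has by then been withdrawn.

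**Working it through.** **1. Is there any route to stay in follow-up off drug?** At the Day 7 call the options are to continue (with the dose increase) or to be withdrawn. At the mid-course call the stated possibility is exclusion from continuing in the study. Neither section offers stopping the drug with follow-up retained, and no other section supplies it.

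**2. Timing of the bloods, Table 2 against Table 3.** Spermidine and fisetin run for 21 days, and 21 + 7 = 28. Metformin runs for 7 + 21 = 28 days, and 28 + 7 = 35. For someone who completes the course, Day 28/35 is therefore one week after the last dose and the tables agree. For early stoppers they do not (the Day 10 and Day 17 calls are read as belonging to the Day 28 and Day 35 schedules):

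| Stops at | Bloods due under Table 3 | Next scheduled venepuncture (Table 2) | Days after stopping |
|---|---|---|---|
| Day 7 (metformin) | Day 14 | Day 35 | 28 |
| Day 10 (spermidine, fisetin) | Day 17 | Day 28 | 18 |
| Day 17 (metformin) | Day 24 | Day 35 | 18 |

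No visit falls on the due date, and the later visit is not available to a participant who has been withdrawn.

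**3. The plan's own figure.** The required 9 cannot be reproduced, because the protocol states no standard deviation, test or sidedness. If a two-sided paired t-test is assumed, 80% power at n = 9 for a difference of 5 implies a standard deviation of change of 4.69. The dropout step does reproduce: 9 / (1 − 0.10) = 10, one spare per sex within each drug.

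**4. Chance of losing more than the one spare.** The withdrawal rate p is assumed. For a cell of 10:

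P(2 or more lost) = 1 − (1 − p)^10 − 10p(1 − p)^9

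At p = 0.10 this is 1 − 0.349 − 0.387 = 0.264. At p = 0.20 it is 1 − 0.107 − 0.268 = 0.624. The chance that at least one of the two metformin cells falls below 9 is 1 − (1 − P)².

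| Assumed withdrawal | One cell below 9 | At least one of two metformin cells below 9 |
|---|---|---|
| 5% | 8.6% | 16.5% |
| 10% | 26.4% | 45.8% |
| 15% | 45.6% | 70.4% |
| 20% | 62.4% | 85.9% |
| 30% | 85.1% | 97.8% |

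These figures matter only if each sex is analysed separately. If 9 are needed per drug out of 20, the count fails only when 12 or more are lost: about 0.01% at 20% withdrawal and 0.5% at 30%.

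**5. Size of the selection (assumed values).** Suppose participants who continue change by 5 points and stoppers by 0. The mean among all who started is 5(1 − w) for a withdrawn fraction w: 4.5 at 10%, 4.0 at 20% and 3.5 at 30%. The mean among those not withdrawn stays at 5 throughout.

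**6. Does keeping stoppers restore power?** Not necessarily. With the implied standard deviation of 4.69 and the same assumption:

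| Stopping | Completers only | All 10, SD 4.69 | All 10, with mixture variance |
|---|---|---|---|
| 10% | n = 9: 80% | mean 4.5: 77% | 73% |
| 20% | n = 8: 74% | mean 4.0: 67% | 60% |

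The mixture variance is 4.69² + 25w(1 − w). Ten participants would give about 85% power only if stoppers responded as fully as the rest.

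**The case against.** The strongest defence is that this is an open-label, uncontrolled Phase 2a mechanistic study. It asks what each agent does after three weeks of intervention. Someone who stops at Day 7 has had one week at the starting dose and cannot supply that measurement, so a completer result may be exactly what is wanted. No between-drug contrast is stated as primary, so uneven loss distorts no stated primary comparison. This has force on the choice of analysis set, which belongs in the SAP. It does not justify failing to collect the data: keeping stoppers in follow-up still allows a completer analysis, whereas withdrawing them allows nothing else.

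Two stronger readings are tempting and the protocol does not support them.

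- *A reader might infer that early stoppers simply miss their safety bloods.* Table 3 does not say so. Read literally, it gives them bloods after discontinuation. Section 10 also follows adverse events unresolved at a participant's last visit until resolution or for up to 30 days. The defect is that Tables 2 and 3 conflict, not that the protocol denies these bloods.
- *A reader might infer that the primary outcome is measured only in those who tolerate treatment.* The mid-course rule is permissive, the Day 7 rule applies to metformin alone, and participants who take the drug poorly or stop without telling the team can still attend Day 28/35, where tablets are counted. The accurate statement is that the outcome comes from those not withdrawn.

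The objection that the loss rates are assumed also stands. The relative risk of 2.445 in section 9 is for diarrhoea, not for withdrawal, and the slow start of metformin is meant to limit side effects.

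**Conclusion.** The point holds in a limited form. As written, stopping the drug at a call is handled as leaving follow-up. Participants withdrawn in this way have no post-treatment biopsy, and metformin carries one additional side-effect-driven exit. For early stoppers, Table 3 promises bloods that no visit in Table 2 delivers.

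The size is uncertain because the protocol gives no withdrawal rate. The 26% and 62% figures illustrate assumed rates of 10% and 20% and apply only to sex-specific analysis. Loss of power is not the main argument, since retaining stoppers may dilute the estimated effect. The argument is that selection becomes visible and that those who had side effects remain under observation. Both depend on data that cannot be recovered after the event.

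**What to change.** - In section 7 (Adverse Event Reporting) and section 11 (Drug Intervention), define two separate events: stopping study drug, and withdrawing from the study.
- State that a participant who stops the drug remains in the study unless consent is withdrawn, and is invited to the already planned Day 28/35 visit for bloods, adverse events and, if willing, the biopsy.
- Reconcile Tables 2 and 3 on bloods after early discontinuation, including the vitamin B12 check. The Day 28/35 visit alone does not meet Table 3's one-week interval for early stoppers, so the tables must be made to agree.
- Report the primary outcome with and without stoppers. Leave the choice of primary analysis set to the SAP.

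The cost is an amendment to the protocol and information sheet. The Day 28/35 visit is already planned; any additional blood sample depends on how the tables are reconciled. Some stoppers will decline the second biopsy, and including those who accept may dilute the estimated effect. The change should be made while recruitment is open. It proposes no dose and no stopping rule, and leaves the sample size as it is.
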